### Participants

This study will be conducted in the Department of Oncology, Guang’an men Hospital, China Academy of Chinese Medical Sciences. Each member of staff of the study team will be able to enroll participants. Inclusion criteria will be as follows: 1) histologically diagnosed with Stage I–IIIA NSCLC according to the 7th edition cancer staging manual of the American Joint Committee on Cancer [23] and had received surgical therapy; 2) had survived no more than 6 months since surgery; 3) Karnofsky performance status of at least 70% at study entry; 4) estimated life expectancy ≥ 6 months; and 5) aged between 18 and 65 years. All study subjects will meet all five inclusion criteria.

Exclusion criteria will be as follows: 1) subjects with serious systemic diseases, such as cerebrovascular, liver, kidney, hematopoietic system, and psychiatric diseases; 2) unable to participate in an exercise training because of either bone or joint diseases; 3) patients who are in other clinical trials; and 4) unable to understand Chinese. Every enrolled patient will sign an informed consent (seen in Additional file 2) before taking part in the later project procedures.

Measures to guarantee adequate participant enrolment will include: 1) a free rehabilitation and exercise training program; 2) the offer of priority access to specialist consultation; and 3) additional general guidance and disease consultation.

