### Randomization and blinding

After completing baseline testing, each participant will be randomly allocated in a 1:1 ratio to either the TCC group or the placebo group. Each participant will learn of their group assignment by receiving a sequentially numbered and sealed opaque envelope from the project director and opening the envelope that contains the group assignment randomly assigned to their sequence number as randomly generated by the computer. Measurement technicians who are responsible for data collection and coding data are blinded to participant group assignment. In addition, all study personnel conducting the study assessments at baseline and postintervention will be blinded to treatment assignment for the duration of the study.

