### Statistical analysis

This randomized trial will recruit 120 subjects with postsurgical NSCLC. Unpaired *t* tests will be used to analysis the primary and secondary endpoints by comparing the TCC to the placebo group regarding mean improvement. We assume that improvement in VO_2peak_ in the TCC group will be 22.5%, while it will be 5% in the placebo group, as reported previously [15]; thus, a minimum of 55 patients per group will be required. Accounting for a 10% dropout rate, the inclusion of 60 patients per group results in a total of 120 patients.

The principal analysis of the study endpoints will employ the intention-to-treat (ITT) approach. The ITT analysis will include all randomized participants in the random allocation. The intervention group assignment will not be altered based on the participants’ adherence to the randomly allocated study arm. Patients who are lost to follow-up will be included in all primary and secondary analyses by assuming zero change across time. For the primary analysis, a multiple regression model will be used to regress change in VO_2peak_ on study group, the baseline value of the endpoint, and other pertinent baseline variables that may influence change in the study endpoints (e.g., co-morbid conditions/medications, self-reported exercise history, age).

All statistical analysis will be conducted using SPSS 17.0 statistics software. The data of all the endpoints are quantitative data. The mean ± standard deviation will be used to describe symmetric data validated by distribution pattern and homogeneity of variance, otherwise the interquartile range (IQR) will be used. If the data are symmetric after being validated by distribution pattern and homogeneity of variance, a *t* test will be used to compare the differences between the quantitative indices between the groups, otherwise the Wilcoxon rank-sum test will be used. For each endpoint, the overall alpha level will be controlled at a one-sided 0.05 by using Holm’s procedure [37]. The collected data will be examined, and the researchers will be supervised to control bias.

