## Discussion

Surgical removal is the best curative option for patients with early-stage NSCLC and for appropriately selected patients with locally advanced disease. Increasing numbers of patients are eligible for receiving surgical intervention [5]. Despite the possibility of a cure, NSCLC survivors with lung resection surgery are often deconditioned and may have varying degrees of impairment of exercise capacity [38] and HRQoL [39] due to the unique pathophysiology of NSCLC, conventional therapeutic strategy, and physical inactivity. Additionally, studies conclude that operable NSCLC patients are at a higher risk of developing emotional distress than other diagnosis groups [40]. Surgically treated NSCLC patients are reported to suffer from persistent physical functional impairment lasting up to 12 months after surgery or longer [41]. Recently, epidemiologic studies and findings suggest that regular exercise can decrease the cancer-related mortality and all-cause mortality among cancer survivors [42], and has been identified as a successful intervention to improve physical and psychological health in some cancer populations (mainly breast cancer) [43]. In light of the increase in the diagnosis of people with curable lung cancer, with the likelihood of an anticipated changing landscape of cancer care, exercise intervention for this population needs to be explored urgently.

TCC, a traditional Chinese exercise, has gained a lot of attention in clinical and research applications as a rehabilitation method for cancer survivors. Recent systematic reviews have demonstrated that TCC may have enormous potential as an effective and feasible rehabilitation intervention to improve tolerance of exercise capacity, symptoms, and immunity function for cancer survivors [18, 19]. In addition, TCC is one of the most common forms of exercise among Chinese adults [20] indicating that there is a large potentially eligible population that would be able to be recruited in to the trial.

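### Entering every patient lost to follow-up as zero change biases the treatment contrast, and not reliably in the conservative direction

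*Protocol article*

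**What the plan says.** The rule stands in the Statistical analysis section of the Protocol article: "Patients who are lost to follow-up will be included in all primary and secondary analyses by assuming zero change across time". It sits inside an intention-to-treat principal analysis of all randomised patients, and the article gives no other rule for missing values. The primary model regresses change in VO2peak on group, baseline value and other baseline variables, so the imputed zeros enter it as outcomes.

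The same section gives the planning figures: "We assume that improvement in VO_2peak_ in the TCC group will be 22.5%, while it will be 5% in the placebo group, as reported previously"; "a minimum of 55 patients per group will be required"; and "Accounting for a 10% dropout rate, the inclusion of 60 patients per group results in a total of 120 patients". The overall alpha is a one-sided 0.05 for each endpoint. The Randomization and blinding section fixes 1:1 allocation.

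**The concern.** Zero change is a specific assumption about patients nobody has measured, and it differs from the mean change that the plan expects in either arm. An imputed constant pulls each arm's mean towards zero in proportion to that arm's loss. Under a real effect this distorts the estimated size of benefit even when loss is balanced. Under no effect, it produces a difference whenever loss is unbalanced and the outcome drifts over time. The rule covers the primary endpoint and every secondary endpoint, so the published effect sizes depend on it throughout. It is often defended as conservative, which needs checking.

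**Working it through.** **Inputs from the document.** Planned mean change 22.5% (TCC) and 5% (control), a difference of 17.5 points; 55 evaluable and 60 enrolled per arm; 10% dropout; one-sided alpha 0.05. The sums use the percentage scale of the sample-size statement.

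**Input not in the document: the SD.** The 55 per arm cannot be reproduced as a comparison of means, because neither SD nor power is given. Solving n = 2(z_alpha + z_beta)² SD² / 17.5² for n = 55 gives:
- one-sided 0.05: SD 36.9 at 80% power, 31.4 at 90%;
- two-sided 0.05: SD 32.8 at 80% power, 28.3 at 90%.

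The working range is therefore 28 to 37 points. A single value of 32.4, inside that range, is assumed where one is needed.

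**General bias formula.** Let dT and dC be the fractions lost, and LT and LC the true mean changes of the lost patients. Setting these to zero gives bias = dC × LC − dT × LT.

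**1. Planned effect, lost patients change like their arm** (LT = 22.5, LC = 5). Expected contrast = 22.5(1 − dT) − 5(1 − dC).

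| Loss TCC / control | Contrast | Bias |
|---|---|---|
| 10% / 10% | 15.75 | −1.75 |
| 20% / 20% | 14.0 | −3.5 |
| 15% / 5% | 14.375 | −3.125 |
| 5% / 15% | 17.125 | −0.375 |
| 0% / 20% | 18.5 | +1.0 |

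The bias is zero only when dC/dT = 22.5/5 = 4.5. Beyond that ratio it favours TCC.

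**2. Interval coverage of the planned 17.5** (SD 32.4, SD² = 1049.76). Per-arm variance of the imputed data = (1 − d)SD² + d(1 − d)m², where m is the arm's mean change.
- 10% loss: TCC 944.78 + 45.56 = 990.35; control 944.78 + 2.25 = 947.03. SE = √(1937.38/60) = 5.68. Bias/SE = 1.75/5.68 = 0.31, so coverage is about 94%.
- 20% loss: TCC 839.81 + 81 = 920.81; control 839.81 + 4 = 843.81. SE = √(1764.62/60) = 5.42. Bias/SE = 3.5/5.42 = 0.65, so coverage is about 90%.

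**3. No treatment effect, common change +5%.** Spurious difference = 5 × (dC − dT).
- 5% TCC / 15% control: 5 × 0.10 = 0.5 point. At SD 28.3 the SE is 4.91, so the one-sided error is 1 − Φ(1.645 − 0.5/4.91) = 6.1%. At SD 36.9 the SE is about 6.39 and the error 5.9%. Simulation with 60 per arm gives 6.0 to 6.2% over the range.
- 10% in each arm: bias 0 and simulated error about 5.0%, so the nominal level is kept.

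**4. Lost patients truly deteriorate** (assumed −10% in both arms), loss 15% TCC / 5% control, observed patients as planned.
- True contrast: (22.5 × 0.85 − 10 × 0.15) − (5 × 0.95 − 10 × 0.05) = 17.625 − 4.25 = 13.375.
- Contrast under the rule: 19.125 − 4.75 = 14.375.
- Bias: +1.0 point towards TCC.

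**The case against.** Much of the case for the plan stands. Where TCC works and loss is roughly balanced, the rule works against TCC. On the plan's own figures the false-positive excess is about one percentage point, and the spurious difference is 0.5 point beside a planned 17.5. Nothing shown predicts unequal loss: both arms have the same session schedule and the same adherence measures.

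Four stronger readings are tempting, and the document does not support them.

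- *The standard errors are wrong.* A reader might set the zero-rule SE (5.68 at 10% loss, SD 32.4) beside the SE from observed patients (32.4 × √(2/54) = 6.24) and call it about 9% too small. Those belong to different estimators. In simulation, the contrast under the rule has a sampling SD of about 5.7, which matches its reported SE. The estimate shrinks along with it: 15.75/5.68 = 2.77 against 17.5/6.24 = 2.81. What remains is biased means and the mild undercoverage shown above.
- *The plan contradicts itself.* The 22.5% and 5% are sample-size assumptions about arm means. They do not say how patients who leave would have changed. Zero is a poor assumption beside them, not a logical contradiction.
- *Error rates could be far higher.* That needs common changes near ±20%, loss of 25% in one arm, or an SD near 15. The document supports none of these. Nor does its remark in the Discussion on "persistent physical functional impairment lasting up to 12 months after surgery or longer" show that scores will move over time.
- *Patients who die are scored as unchanged.* Inclusion criterion 4 under Participants sets "estimated life expectancy" at a minimum of 6 months, and the study runs 12 months, so a reader might infer this. But the minimum is not an expected survival, and the article does not say that deaths count as lost to follow-up. The wording leaves the matter open, which is reason enough to state it.

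**Conclusion.** The concern holds at moderate size; the rule should be fixed but does not invalidate the trial. Zero-change imputation biases the contrast by −1.75 points at 10% loss per arm and −3.5 at 20%, provided lost patients would have changed like their arm. With no effect and unequal loss it can raise the one-sided error slightly, to about 6% at 5%/15% loss. It cannot be relied on as conservative: it favours TCC if control loss exceeds 4.5 times TCC loss under the planned effect, or if more TCC patients are lost and they truly decline.

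The SD range is back-calculated from n = 55. The splits of loss between arms and the 10% decline are illustrative assumptions.

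**What to change.** Replace the sentence in the Statistical analysis section. The primary analysis should keep all randomised patients in their allocated arm and handle missing values by one of two routes, named in advance:

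- a likelihood-based repeated-measures model using baseline and all observed visits; or
- multiple imputation within arm, using baseline values and all observed visits.

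State that deaths are reported separately and not scored as unchanged. Keep zero change as one labelled sensitivity analysis. That is useful because both replacement methods also rest on an untestable assumption about the lost patients.

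The change needs no new patients or visits and preserves intention-to-treat. It costs a little more programming and a slightly larger SE. At 10% loss and SD 32.4 the SE would be about 6.24 instead of 5.68 if the baseline and other visits recovered no information. The ratio of expected effect to SE would hardly move (2.81 against 2.77).

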#### Secondary endpoints

The secondary endpoints of this trial will be the 6-min walk distance (6MWD), lung function, patient-reported outcomes, and immunity function.

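### Secondary endpoints: a baseline-adjusted regression, as already planned for VO2peak, would be more precise than the t test or Wilcoxon choice and would keep mean improvement as the target

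*Protocol article*

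**What the plan says.** The Statistical analysis section of the protocol article makes three statements that bear on this point.

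- One rule, naming the unpaired t test, covers all endpoints: "tests will be used to analysis the primary and secondary endpoints by comparing the TCC to the placebo group regarding mean improvement".
- The choice of test depends on a check of the trial data. The condition is worded "If the data are symmetric after being validated by distribution pattern and homogeneity of variance". What follows from passing or failing that check is stated next: "test will be used to compare the differences between the quantitative indices between the groups, otherwise the Wilcoxon rank-sum test will be used".
- The covariate-adjusted model is tied to one endpoint, VO2peak: "For the primary analysis, a multiple regression model will be used to regress change in". Its regressors are described separately as "on study group, the baseline value of the endpoint, and other pertinent baseline variables".

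The Secondary endpoints section lists what falls outside that model: "The secondary endpoints of this trial will be the 6-min walk distance (6MWD), lung function, patient-reported outcomes, and immunity function". The Abstract and the Study design and procedures section both place a baseline measurement on these endpoints. On error control, for which Holm's method is named, the Statistical analysis section says: "For each endpoint, the overall alpha level will be controlled at a one-sided 0.05 by using". It mentions no unequal-variance t test.

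**The concern.** Two features of the stated method work against the secondary results.

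First, the protocol uses the baseline value as a covariate for VO2peak but not for walk distance, lung function, patient-reported outcomes or immune measures, although their baselines are collected. Subtracting the baseline, as an improvement score does, uses that information less efficiently than regressing on it.

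Second, failed homogeneity of variance leads to the Wilcoxon rank-sum test. With unequal spreads, that test no longer addresses the difference in mean improvement that the protocol names. If the data are also skewed, it can reject when the means are equal. In addition, some endpoints would be reported as a mean difference and others as a rank result, with the choice made after the data are seen.

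**Working it through.** **Plan's own figure.** No sample size or precision is given for any secondary endpoint. The 55 per group is for VO2peak and cannot be reproduced, because neither an SD nor a power is stated. The check therefore takes the planned 60 per arm and 1:1 allocation from the article. The correlation r, the SD ratios and the shape of the distributions are assumptions.

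**Step 1: precision.** Take equal baseline and follow-up SDs (scaled to 1) and correlation r.

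- Variance of change = 2(1 − r).
- Residual variance after regression on baseline = 1 − r².
- Ratio = (1 − r)(1 + r) / [2(1 − r)] = (1 + r)/2.
- Change-score interval relative to ANCOVA = 1/√[(1 + r)/2].
- If the change-score test has 80% power at one-sided 0.05, ANCOVA power = Φ[(1.645 + 0.842)/√((1 + r)/2) − 1.645].

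| Assumed r | Variance ratio | Change-score interval wider by | ANCOVA power |
|---|---|---|---|
| 0.3 | 0.65 | 24% | 92.5% |
| 0.5 | 0.75 | 15% | 89.0% |
| 0.7 | 0.85 | 8% | 85.4% |
| 0.9 | 0.95 | 3% | 81.8% |

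**Step 2: the gate.** Simulations used 60 per arm, equal true means, and normal or gamma (shape 2) data. The gate was a median-centred Levene-type variance test at 5%, choosing the pooled t test or Wilcoxon. The main run had 40,000 replicates, and a repeat had 20,000. Two-sided rejection at nominal 5%:

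| Data | SD ratio | Wilcoxon alone | Gated procedure | Welch |
|---|---|---|---|---|
| Normal | 1.5 | 5.3% | 5.1% | 5.0% |
| Normal | 2 | 5.7% | 5.7% | 4.9% |
| Skewed | 1.5 | 13.8% | 6.8% | 5.0% |
| Skewed | 2 | 24.0% | 22.9% | 5.4% |

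Across runs, the gated skewed figure at ratio 2 lay between 22% and 23%. With normal data the gate sends 80% of trials to Wilcoxon at ratio 1.5 and 99.7% at ratio 2, so the fallback would be used often if spreads differed that much.

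**Step 3: at the protocol's one-sided 0.05.** With right skew, the gated procedure rejects in favour of the more variable arm 0.8% of the time at ratio 1.5 and 0.4% at ratio 2. In favour of the less variable arm it rejects about 12% and 32 to 34%. Reversing the skew swaps these. If TCC is the more variable arm and has a tail of large gains, the procedure is very conservative for a TCC benefit. If TCC has a tail of poor responses, it is anti-conservative.

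**Step 4: what the simulated gate covers.** It represents the variance check only. The article also names a symmetry check but no test for it. When a skewness test at 5% in each arm was added, nearly all skewed trials went to Wilcoxon and the two-sided figure at ratio 1.5 returned to 13.8%. The 7% therefore belongs to a variance-only gate.

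**The case against.** The strongest reply is that the planned comparison is not wrong. A reader might infer that the secondary endpoints get no baseline adjustment at all. The article does not support that: improvement already subtracts the baseline, and in a randomised trial the change-score comparison is unbiased. Only covariate adjustment is absent. Its value depends on a correlation that the article does not give, and it is slight near r = 0.9. This stands.

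A reader might also take the Wilcoxon-alone rates as the error of the plan. They are not, because a gate precedes the test. With symmetric data the excess is negligible. With skew at ratio 1.5, a variance-only gate gives about 7%. The rates are also two-sided, whereas the protocol tests one-sided, and if a few TCC patients respond strongly the procedure is conservative for TCC. This stands too, with the caveat that an active symmetry check would move the 7% back towards 14%.

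Finally, a reader might infer that imputing zero change makes the spreads unequal. That is not shown. As an illustration, take the VO2peak means (improvement "in the TCC group will be 22.5%, while it will be 5% in the placebo group"), 10% imputed zeros in each arm, and a common SD s among completers. The variance is 0.9s² + 0.09m², where m is the arm mean. The n of 55 implies s = 17.5 × √(55/2) / (z_α + z_β), which runs from 28.3 (two-sided 0.05, 90% power) to 36.9 (one-sided 0.05, 80% power).

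- s = 28.3: √[(720.8 + 45.6)/(720.8 + 2.3)] = 1.03.
- s = 36.9: √[(1225.4 + 45.6)/(1225.4 + 2.3)] = 1.02.

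With equal means and equal dropout, the zeros create no difference in spread.

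The reply does not remove two facts. The fallback changes the quantity being tested, and the more precise model is already in the protocol for VO2peak.

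**Conclusion.** The point holds as a free improvement for the secondary endpoints. It is not an error that invalidates them, and it does not touch the primary result.

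The precision gain is certain in direction for any r below 1 under equal SDs, but its size is unknown: intervals are 15% to 3% wider than needed for r between 0.5 and 0.9. The loss of error control for a mean difference is real only when unequal spread and skew occur together. Nothing in the article documents either for these endpoints, so the SD ratios of 1.5 and 2 are scenarios, not forecasts. At 1:1 allocation the pooled t test itself held 4.9 to 5.6% two-sided in every scenario simulated (SD ratios 1 to 3), so the variance gate protects against very little.

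This is not a matter of detail left to an unseen analysis plan. The article states the test, the gate and the fallback, and it restricts the adjusted model to VO2peak.

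**What to change.** For each secondary endpoint, regress change on study group and that endpoint's own baseline value, as already planned for VO2peak, with heteroscedasticity-robust standard errors. Report the adjusted mean difference with its confidence interval. Remove the distribution and variance check as a means of choosing the test, and keep the Wilcoxon rank-sum test as a sensitivity analysis only.

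A repeated-measures model across visits is not needed for this purpose. It would have to be reconciled with the stated rule that patients lost to follow-up are assigned zero change.

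The cost is analysis wording and programming, including a check that the named software provides robust standard errors. No new data are needed, so completed recruitment is no obstacle. The change should be recorded before outcome data are compared by arm.

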## Discussion

Surgical removal is the best curative option for patients with early-stage NSCLC and for appropriately selected patients with locally advanced disease. Increasing numbers of patients are eligible for receiving surgical intervention [5]. Despite the possibility of a cure, NSCLC survivors with lung resection surgery are often deconditioned and may have varying degrees of impairment of exercise capacity [38] and HRQoL [39] due to the unique pathophysiology of NSCLC, conventional therapeutic strategy, and physical inactivity. Additionally, studies conclude that operable NSCLC patients are at a higher risk of developing emotional distress than other diagnosis groups [40]. Surgically treated NSCLC patients are reported to suffer from persistent physical functional impairment lasting up to 12 months after surgery or longer [41]. Recently, epidemiologic studies and findings suggest that regular exercise can decrease the cancer-related mortality and all-cause mortality among cancer survivors [42], and has been identified as a successful intervention to improve physical and psychological health in some cancer populations (mainly breast cancer) [43]. In light of the increase in the diagnosis of people with curable lung cancer, with the likelihood of an anticipated changing landscape of cancer care, exercise intervention for this population needs to be explored urgently.

TCC, a traditional Chinese exercise, has gained a lot of attention in clinical and research applications as a rehabilitation method for cancer survivors. Recent systematic reviews have demonstrated that TCC may have enormous potential as an effective and feasible rehabilitation intervention to improve tolerance of exercise capacity, symptoms, and immunity function for cancer survivors [18, 19]. In addition, TCC is one of the most common forms of exercise among Chinese adults [20] indicating that there is a large potentially eligible population that would be able to be recruited in to the trial.

The main outcome of the present trial is exercise capacity. The gold standard for measurement of exercise capacity is a direct measure of VO_2Peak_; other testing methods include the 6MWD, shuttle walk test, and stair-climbing test. Among these, VO_2peak_ and 6MWD are the two most frequently used (52% and 16%) [44]. Furthermore, VO_2Peak_ is an independent predictor of all-cause pulmonary morbidity [45, 46]. Brunelli and colleagues found that a VO_2Peak_ of no less than 20 mL/kg/min is a safe cutoff value, and no mortality was observed above this threshold for major lung resection [47]. Consistent with this, the findings of Jones et al. suggest that higher VO_2peak_ was associated with a statistically significant 21% to 24% reduction in the risk of mortality, and a VO_2peak_ of < 14 mL/kg/min may identify patients with poor prognosis [48]. Together, this indicates that VO_2peak_ is an emerging evaluating parameter of exercise training in patients with NSCLC. Specifically, research has shown TCC to be beneficial to the VO_2peak_ of middle-aged subjects [49, 50]. Despite the wealth of evidence, research has seldom explored the efficacy of TCC against exercise capacity or VO_2peak_. Thus, the primary outcome of this trial will be VO2peak. 6MWD and lung function will be set as simple and alternative elements to comprehensively assess the exercise capacity of this specific population.

Patients with operable NSCLC also experience fatigue and dyspnea, and are at risk for developing psychosocial problems, reduced quality of life as well as immune function. And, existing evidence have suggested that TCC has a promising function on enhancing proliferative and cytolytic activities of peripheral blood mononuclear cells (PBMCs), as well as increasing the ratio of T helper/T suppressor cells and mediating Th1/Th2 T-helper cell balance in postsurgical NSCLC patients, thus improving the immunity function of the patients [51, 52]. Therefore, our study also takes above symptom and immunity parameters into consideration to comprehensively evaluate the clinical benefit of TCC as an exercise intervention.

To enable TCC intervention to be integrated into clinical practice, it is important to determine the optimal design of TCC intervention that will be feasible, acceptable, and positively affect outcomes in a healthcare setting as rehabilitation in postsurgical patients with NSCLC in a randomized clinical trial. To our knowledge there are currently no clinical trial focusing on TCC intervention for surgically treated NSCLC patients. Therefore, the results of this study will offer an overview of the possible effects of TCC and address many critical unknown questions in order to set the stage for more clinical trials using traditional Chinese exercises such as Qigong and Baduanjin. In the long term, we are looking forward to making a contribution to the establishment of exercise interventions as a non-pharmacologic therapeutic guideline for NSCLC patients.

While the trial will potentially significantly contribute to these fields of research, potential limitations of the study should also be recognized. One difficulty encountered in the design of the trial was selecting an appropriate control condition. There were several options for control participants including: 1) strength training; 2) conventional aerobic exercise; and 3) stretching placebo. Although the first two of these have shown clinical benefit for NSCLC, neither of them was selected. Strength training was not selected because it is too vigorous and unacceptable for NSCLC based on our prior oral pilot questionnaire. Furthermore, the target of the trial is to explore the clinical efficacy and feasibility of TCC, rather than the comparison between TCC and aerobic exercise; thus, stretching as a more tolerable and safe control was selected.

